## Abstract

**Introduction:**

Diabetes and hypertension are prevalent and costly to the health system. We have developed a mobile app (EMPOWER app) which enables remote monitoring and education through personalised nudges. We aim to study the effectiveness of a multi-component intervention comprising the EMPOWER mobile app with health coaching and shared decision-making for diabetes and hypertension.

**Methods:**

We will conduct a two-arm, open-label, pragmatic randomised controlled trial (RCT). Participants with comorbid diabetes and hypertension enrolled from public primary care clinics will be randomised to either intervention or control in a 1:1 ratio. The intervention group participants will have access to health coaching with shared decision-making interventions in addition to the EMPOWER app and their usual primary care. The control group participants will continue to receive usual primary care and will neither receive the EMPOWER app nor health coaching and shared decision-making interventions. Our primary outcome is change in HbA1c level over 9 months. Secondary outcomes include change in systolic blood pressure, quality of life, patient activation, medication adherence, physical activity level, diet, and healthcare cost (direct and indirect) over 9 months.

**Discussion:**

Our trial will provide key insights into clinical- and cost-effectiveness of a multi-component intervention comprising EMPOWER mobile app, health coaching and shared decision-making in diabetes and hypertension management. This trial will also offer evidence on cost-effective and sustainable methods for promoting behavioural changes among patients with comorbid diabetes and hypertension.

**Trial registration:**

This study was registered on clintrials.gov on August 3, 2022, with the trial registration number: NCT05486390.

## Introduction

Diabetes and hypertension are prevalent chronic diseases worldwide, with 537 million adults having diabetes worldwide [1] and the age-standardised prevalence of hypertension being around 30% globally [2]. Moreover, these diabetic and hypertensive patients are at greater risk for microvascular and macrovascular complications [3], including elevated rates of cardiovascular death and myocardial infarction [4]. It is well-established that lifestyle improvements in dietary habits and physical activity are effective in improving outcomes of both diabetes [5] and hypertension [6, 7]. However, due to the time constraints [8, 9], promotion of healthier lifestyle changes in conventional healthcare settings is difficult [10].

Mobile health (mHealth) can be an effective solution to promote lifestyle modification among patients with comorbid diabetes and hypertension. Previous reviews have shown that mHealth interventions may be effective for improving patient outcomes among patients with diabetes or hypertension [11, 12]. However, limited evidence exists for effectiveness of mHealth intervention for patients with comorbid diabetes and hypertension [11, 13]. We have developed a novel mobile app (EMPOWER app) which enables remote monitoring and education of patients with diabetes through personalised nudges. The effectiveness and implementation of the EMPOWER app in improving diabetes self-management is being evaluated in an ongoing randomised controlled trial [14]. However, numerous trials have shown that patient self-monitoring alone may have a limited effect on improving blood pressure control for patients with comorbid conditions [15–17]. To effectively combat the comorbid condition of inadequate blood pressure management [18, 19], it is important to develop an innovative care model that involves multiple components including mHealth solution, health coaching and shared decision making.

Therefore, we aim to study the effectiveness of the EMPOWER mobile app in conjunction with health coaching and shared decision-making in patients with comorbid diabetes and hypertension through a randomised controlled trial (RCT). The findings from this study may provide evidence for better management and care model for patients with comorbid diabetes and hypertension. This protocol paper details the study design and planned analyses, and is based on protocol version 2 dated 1 October 2022.

## Methods

### Study design

We will execute an open label, two-arm, parallel randomised pragmatic trial. The pragmatic study design is based on the Pragmatic Explanatory Continuum Indicator Summary Framework-2 (PRECIS-2) criteria [20]. We will randomly allocate eligible and consented participants in a 1:1 ratio to either intervention or control group. The intervention participants will have access to (1) EMPOWER mobile app, (2) Fitbit tracker and Fitbit app, (3) health coaching, (4) shared decision making, and (5) usual primary care. The control group participants will get Fitbit tracker, Fitbit app and usual primary care only (Fig 1). This study protocol is written according to the Standard Protocol Items: Recommendations for Interventional Trials (SPIRIT) reporting guidelines [21] (Fig 2 and S1 File: SPIRIT 2013 Checklist). Participant recruitment has commenced on 17 February 2023, but has not been completed at the time of manuscript submission and publication.

**Fig 1 pone.0296338.g001:**
[figure not shown]
Trial work plan. Follow- up will be performed at month 3, 6 and 9.

**Fig 2 pone.0296338.g002:**
[figure not shown]
SPIRIT figure for the schedule of enrolment, interventions, and assessments. Abbreviation: EQ-5D-5L: EuroQoL-5 Dimensions; HbA1c: Haemoglobin A1c; PAM: Patient Activation Measure. * Only for participants randomized to intervention group.

### Ethics and dissemination

Ethics approval was granted (Reference number: 2022/2326) by the SingHealth Centralised Institutional Review Board. In addition, the board oversees protocol amendment, adverse event reporting and review. Written informed consent will be obtained from all participants prior to study commencement. The informed consent document can be found in the S2 File: Consent form. Payment and compensation of injuries and illness to participants arising from participation in this study will be assessed by the study team, and will be covered as per guidelines under the National Clinical Trials Insurance policy that SingHealth subscribes to.

Study findings will be disseminated through presenting at international conferences as well as publishing in peer-reviewed journals. The authorship will be finalised by the overall principal investigator ([name]) according to the International Committee of Medical Journal Editors (ICMJE) guidelines. The study team does not intend to engage professional writers for this study.

### Inclusion and exclusion criteria

Patients are recruited from three polyclinics in Singapore, which are public healthcare centres providing subsidised primary care. The trial inclusion criteria at the time of recruitment are:

(1) Aged 21 years and older,(2) Has a diagnosis of diabetes,(3) Haemoglobin A1c (HbA1c) ≥ 7.0% (most recent result),(4) Systolic blood pressure≥ 140 mmHg or diastolic blood pressure ≥ 90 mmHg on two or more prior visits, physician-diagnosed hypertension, or on antihypertensive medication,(5) Able to exercise physically,(6) Literate in English.

We will exclude patients who at the time of recruitment:

(1) Require aid with basic activities of daily living,(2) On bolus insulin,(3) Have upcoming major medical or surgical procedure during the trial,(4) Impaired cognitively [22].

### Intervention

The EMPOWER app has been described in detail in an earlier paper (14). The key features and functionalities of the EMPOWER app include (1) Personalised nudges based on Artificial Intelligence (AI) learning of the participant’s behaviour, (2) Gamification, (3) Logging and report, (4) Educational resources, which are mapped to key domains and interventions in the Behavioural Change Wheel (BCW) (S3 File: EMPOWER app features) [23].

The intervention group participants will interact with health coach throughout the study duration. The health coach involved in this study will include a registered nurse under the telecare service unit in an acute hospital. The health coach will contact the intervention group participants via phone call, videocall and/ or text messages. In this study, the health coach will be responsible for the following roles [24]:

(1) Goal setting and action plan: Health coach will discuss the goals of treatment, and the reason for these goals. The health coach will discuss lifestyle factors influencing response to treatment of diabetes, hypertension and/or hyperlipidemia (e.g., salt or carbohydrate intake, weight, and physical activity). The health coach will also discuss with the participants regarding their willingness to modify these lifestyle factors, and propose a customised action plan for each participant. The health coach will also prepare a tailored education program consisting of information about the risks of diabetes, hypertension and/or hyperlipidemia as well as the advantages of treatment and lifestyle changes.(2) After-visit summary: After consultation with physician, health coach will ask participants whether there is anything they would like to discuss. Health coach will generate an after-visit summary to recap the advice given by the physician during the visit, including behaviour changes plan, medication plan, and subsequent follow-up date. Health coach will also make sure that participants are able to navigate the health system to accomplish the agendas in the after-visit summary.

A report card summarising the lifestyle behaviour (including diet, physical activity and weight), goals and action plans will be made available in the app to facilitate shared decision making.

### Control

The control group participants will get Fitbit tracker and the Fitbit app but will have no access to the EMPOWER app, health coach nor shared decision making. This will allow investigation of the effectiveness of the EMPOWER mobile app in conjunction with health coaching and shared decision making in patients with comorbid diabetes and hypertension.

### Outcome measures

Our primary outcome is change in HbA1c level over 9 months (Table 2). The measurement of glycated haemoglobin using HbA1c is widely accepted as a standard index of glycaemic control of diabetic patients [25]. HbA1c will be measured using platforms available at the in-house laboratory at the study sites, and the platforms will be National Glycohemoglobin Standardization Program-certified.

Our secondary outcomes will include change in systolic blood pressure, quality of life (QoL), patient activation, medication adherence, physical activity level, diet, and healthcare cost (direct and indirect) over 9 months. The outcome measures are listed in Table 1. We will extract healthcare cost from electronic medical records, and supplement with survey data on self-reported income, travel cost, and employment status.

**Table 1 pone.0296338.t001:** Outcome measures to evaluate clinical and cost-effectiveness.

Variables	Source and Measure/ Instrument name	Time of collection
Primary Outcome Measure		
Haemoglobin A1c (HbA1c)	Platforms available at the in-house laboratory at polyclinics	Baseline, 3, 6, and 9 months
Secondary Outcome Measures		
Systolic blood pressure	Devices available at polyclinics	Baseline, 3, 6, and 9 months
Physical activity	Smartwatch: steps taken, active minutes, sleep quality, sleep time and heart rate	Baseline (first 2 weeks), and real-time tracking throughout 9-month follow-up
Dietary intake	Mobile application: Calorie intake, carbohydrate intake and sodium intake	Baseline (first 2 weeks), and real-time tracking throughout 9-month follow-up
Patient activation	Survey: Patient activation measure (PAM) [26]	Baseline, 3, 6, and 9 months
Medication adherence	Survey: Voils DOSE-Nonadherence [27]	Baseline, 3, 6, and 9 months
Quality of life	Survey: EQ-5D-5L [28]	Baseline, 6, and 9 months
Direct healthcare cost	Electronic medical records: Costs of consultations, lab tests, medications, admissions	All entries throughout 9-month follow-up
Indirect healthcare cost	Survey: Self-reported income, travel cost, employment status	Baseline, 3, 6, and 9 months

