### Randomization and blinding process

Participants will be randomised to intervention or control group using a computer-generated randomization list provided by the trial biostatistician. We implemented stratified block randomization using randomly varying block sizes with recruitment site and duration of diabetes (<10 years or ≥10 years) as stratification factors based on a 1:1 allocation ratio. The cut-off of 10 years for duration of diabetes is supported by the data from previous studies [32, 33] and local SingHealth Diabetes Registry (mean disease duration ranging from 9.0–11.3 years from 2013 to 2019) [34].

Upon obtaining informed consent and enrolling a participant, the research coordinators at the polyclinic sites will contact a centralised research staff (who oversees the study progress but is not involved in patient recruitment) for the randomisation assignment.

The data analyst will be blinded to the assignment of interventions. It is not possible to blind study participants and care providers to the random assignment due to the nature of the intervention in this study.

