### Statistical analyses

We will summarise participant’s characteristics using median (interquartile range) for non-normally distributed or mean (standard deviation) for normally distributed continuous variables respectively, and count and percentage for categorical variables. We will analyse the primary outcome of change in HbA1c over the 9 months follow-up, using a linear mixed model with adjustment for baseline HbA1c. A further model will be considered to explore whether the treatment effect on HbA1c varies with time, by including the treatment by time interaction, and adjusting for baseline systolic blood pressure and other potential confounders as appropriate via the mixed model.

We will use linear mixed model to account for within-individual correlation among measurements, and the sandwich estimator to obtain robust standard error estimates for secondary outcomes with repeated measurements (e.g., systolic blood pressure, quality of life, patient activation score). Pseudo maximum likelihood estimation method will be used for the parameter estimation. We will include intervention indicator and time factor as predictors, adjusting for the respective baseline covariates. For both the primary and secondary outcomes, alternative models such as mixed effect quantile regression may be considered if the model assumptions are violated.

All evaluations will be made using two-sided p-values at the 5% level of significance. Statistical analyses will be conducted based on the principle of intention-to-treat.

We will also conduct an economic evaluation from the health care system and societal perspectives. We will perform both cost-effectiveness analysis (i.e., cost of reduction in 1% in HbA1c) and cost-utility analysis (cost of reduction in 1 quality-adjusted life year saved).

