### Implementation

We will assess the impact and sustainability of interventions using the RE-AIM framework [35]. Data sources include qualitative focus groups and interviews with a purposive sample of participants and stakeholders, survey data, and electronic medical records. In addition, qualitative interviews will be conducted with a purposive sample of participants to collect their feedback on the EMPOWER app, health coaching and shared decision making interventions in promoting behavior change based on shared domains of the theoretical domain framework [36, 37] and social cognitive theory [38]. Specifically, we will focus on exploring knowledge, skills and reinforcement, self-efficacy, beliefs about consequences (outcome expectation), intention and goals, environmental context and social support/influences (S4 File: Sample interview questions for patients). These domains will assist in identifying cognitive, affective and social/environmental factors influencing behavioral change. In addition to patient interviews, interviews with healthcare professionals (clinician, health coach) and research coordinators will be conducted to elucidate implementation challenges and experiences (S5 File: Sample interview questions for other stakeholders). The details on data sources and parameters assessed for each RE-AIM dimension can be found in Table 2.

**Table 2 pone.0296338.t002:** Data sources and parameters assessed for RE-AIM dimensions.

RE-AIM Dimension	Data source	Parameters
Reach	Demographic data, administrative data, RCT survey data, interviews with stakeholders	Estimated number and percentage of patients with comorbid diabetes and hypertension approached Estimated number and percentage of patients eligible for the study Reasons for refusal to participate Number and percentage of dropouts, and reasons
Effectiveness	RCT survey data, EMR	Clinical measures before and after the intervention: HbA1c to target BP readings to target Long term complications (e.g., Major Adverse Cardiac Events, death, surgery, stroke, amputations, renal failure) Patient activation (Patient activation measure [26]) Physical activity (Wearable data) Medical Adherence (Voils DOSE-Nonadherence [27] and medication logging in EMPOWER app) Dietary changes (Diet logging in EMPOWER app) Quality of life (EQ-5D [28]) Length of stay, hospital-free days Direct healthcare cost, indirect healthcare cost

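### The two-week baseline for physical activity and diet appears to fall after randomisation, so using it as a change reference or covariate would remove any early treatment effect

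*Protocol article*

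**What the plan says.** Table 1 (Outcome measures) gives the clinic and survey outcomes an ordinary baseline assessment. Physical activity and dietary intake are different: their time of collection is "Baseline (first 2 weeks), and real-time tracking throughout 9-month follow-up". Their baseline is thus the opening stretch of the tracking record. The same section defines both outcomes as change over 9 months.

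Four other places bear on when that window falls and how it is used:

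- Randomization and blinding process: "Upon obtaining informed consent and enrolling a participant, the research coordinators at the polyclinic sites will contact a centralised research staff" to obtain the assignment. No interval or run-in is mentioned.
- Study design: the tracker is listed under what each arm receives, for example "The control group participants will get Fitbit tracker, Fitbit app and usual primary care only".
- Intervention: "The intervention group participants will interact with health coach throughout the study duration". No start date is given for coaching or app nudges, and no initial hold.
- Statistical analyses, for secondary outcomes with repeated measurements: "We will include intervention indicator and time factor as predictors, adjusting for the respective baseline covariates".

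The source of the diet data is described in two ways. Table 1 has "Mobile application: Calorie intake, carbohydrate intake and sodium intake" without naming the app. Table 2 (Implementation) has "Dietary changes (Diet logging in EMPOWER app". The Control section says that control participants "will have no access to the EMPOWER app, health coach nor shared decision making".

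**The concern.** A baseline used for adjustment, or as the reference for change, should be fixed before treatment can affect it. If the first two weeks of tracking follow allocation, the intervention arm may already be walking more or eating differently by then. Subtracting or conditioning on that value removes part of the effect the trial wants to measure, and the comparison is no longer protected by randomisation. Activity and diet are behaviours that the app and the coach are meant to change, so a diluted result on them could be misread as the intervention having failed to change behaviour.

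**Working it through.** **Step 1: timing.** No sentence places the two-week window relative to allocation, so the order has to be inferred.

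- Assignment is requested on consent and enrolment.
- The tracker and apps are described as part of each arm's package, so on the visible text tracking starts after the arm is known.
- Coaching covers the whole study, and no hold on coaching or nudges is stated.
- For diet, an entry in the EMPOWER app can exist only after allocation to the intervention arm.

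The visible text therefore points to a window after randomisation. Fig 1 (work plan) and Fig 2 (schedule) are not shown, and Fig 2 could show otherwise.

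**Step 2: what the analysis would estimate.** Let E be the between-arm effect present in the two-week value, L the later effect, and b the within-arm regression slope of later values on the two-week value.

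- Change score: (later difference) − (two-week difference) = L − E.
- Baseline adjustment: (later difference) − b × (two-week difference) = L − bE.

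With f = E/L, the share of the later effect retained is 1 − f for a change score and 1 − bf for adjustment.

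**Step 3: numbers.** The protocol gives no value for E, L or b for these outcomes and no figure to reproduce. Both ranges below are assumptions: f from 0 to 1, and b from 0.3 to 0.8.

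| Early share f | Retained, change score | Retained, adjusted (b = 0.3 to 0.8) |
|---|---|---|
| 0 | 100% | 100% |
| 0.25 | 75% | 92.5% to 80% |
| 0.5 | 50% | 85% to 60% |
| 1 | 0% | 70% to 20% |

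For example, f = 0.5 and b = 0.8 gives 1 − 0.8 × 0.5 = 0.60.

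**Step 4: check by simulation.** There were 2,000 runs with 128 per arm (320 × 0.8 / 2). The shares retained, adjusted then change, were:

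- f = 0: 1.00 and 0.99 at b = 0.375; 1.00 and 1.00 at b = 0.7.
- f = 0.5: 0.82 and 0.51 at b = 0.375; 0.65 and 0.50 at b = 0.7.
- f = 1: 0.63 and 0.02 at b = 0.375; 0.30 and 0.00 at b = 0.7.

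These agree with the formulas. The simulation confirms the algebra. It does not show that an early effect exists in this trial.

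**Step 5: diet.** If Table 2 describes the only diet log, the control arm has no diet series. There is then no between-arm effect to attenuate, and no between-arm comparison of follow-up values is possible. If the app in Table 1 is another one that both arms use, Steps 1 to 3 apply to diet as they do to activity.

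**The case against.** The strongest reply is that the timing is inferred. The protocol gives an order of events but no intervals, and the schedule figure might show tracking before allocation. This stands, and it is why the point is conditional. It does not remove the point, because nothing in the visible text describes a run-in.

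A second reply is that an early effect may be absent. Both arms receive the tracker, so the effect of wearing it is shared. The nudges depend on the app learning each participant's behaviour, which is compatible with an initial period of data gathering. A reader might infer that intervention participants are already being nudged and coached towards goals in weeks 1–2. The documents do not say so, since coaching throughout the study fixes no start date. With E = 0 nothing is lost.

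A third reply is that the model paragraph names blood pressure, quality of life and patient activation as its examples, not activity or diet, and that the way a continuous stream is summarised is commonly left to an analysis plan. This stands in part. The examples are only illustrative, and the definition as change covers both outcomes. The point concerns a baseline window that the protocol does fix, not a missing detail.

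**Conclusion.** The concern holds in conditional form. On the visible text, the two-week baseline for activity and diet appears to come after randomisation. If it does, and if treatment has any effect in that window, taking change from it or adjusting for it subtracts that effect.

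The size cannot be computed from the documents. It runs from no loss (E = 0) to total loss for a change score (E = L); under adjustment with b up to 0.8, at most 80% is lost when E = L. A reader might take the upper end as the expected bias. That would require the full later effect to be present already on average over the first 14 days, and no document supports this.

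A reader might also extend the problem to the main result. It does not reach that far: HbA1c has its own baseline measurement, and neither its model nor the sample size uses the tracking data. The issue is confined to two secondary outcomes. For diet, the prior question is whether control data exist at all.

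**What to change.** State when the two-week window begins relative to allocation and to the first active intervention. If it precedes either, one sentence saying so settles the timing.

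Otherwise, for physical activity, do not use weeks 1–2 as a covariate or as the reference for change. Treat them as the first follow-up period and compare the arms on follow-up values, adjusting only for variables fixed before randomisation, such as site, diabetes-duration stratum, age and baseline HbA1c. This takes a sentence or two of analysis text. The cost is some precision, because no true baseline for activity would be available.

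For diet, first reconcile Table 1, Table 2 and the Control section on which app is used and by whom. If controls log intake in another app, apply the same rule. If they do not, report diet as a description within the intervention arm and not as a between-arm effect. The cost is the loss of diet as a comparative secondary outcome.

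Tracking before randomisation for participants still to be enrolled would give a true activity baseline. However, recruitment has already begun, so it would mix two baseline definitions within the trial and delay allocation by two weeks. The change to the analysis is simpler.

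### EQ-5D-5L is the only Table 1 survey not given at month 3; adding it is a cheap way to stop the QALY result resting on an unobserved 0-6 month path

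*Protocol article*

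**What the plan says.** In Table 1 (Outcome measures), the quality-of-life row has EQ-5D-5L given by survey at "Baseline, 6, and 9 months". The other three survey rows (patient activation, medication adherence, indirect healthcare cost) are collected at "Baseline, 3, 6, and 9 months", as are HbA1c and systolic blood pressure. The Fig 1 caption confirms the contact schedule: "Follow- up will be performed at month 3, 6 and 9". No reason is given for leaving EQ-5D-5L out at month 3. The Fig 2 schedule was not available for comparison.

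The Statistical analyses section uses quality of life twice. It is a secondary outcome with repeated measurements, analysed by linear mixed model. A cost-utility analysis is also planned, with its result described as "cost of reduction in 1 quality-adjusted life year saved". EQ-5D-5L is the only utility instrument listed, so the QALYs must come from it. That link is an inference, but no other source is offered.

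**The concern.** A QALY difference is the area between the arms' utility curves over the nine months. With readings at 0, 6 and 9 months, the first two thirds of that area depends on how baseline is joined to month 6. What happens between those points is not observed, although participants are already surveyed in the middle of the interval.

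The incremental QALY is the denominator of the cost-utility ratio, so an error in it passes straight into the cost per QALY. The quality-of-life outcome also has two post-baseline readings where the other repeated survey measures have three. An analysis plan can choose an interpolation rule, but it cannot recover a month-3 utility that was never measured.

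**Working it through.** The document states no QALY, utility or bias figure, so there is nothing of the plan's own to reproduce.

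**Inputs from the document.** EQ-5D-5L times 0, 6, 9 months; other survey times 0, 3, 6, 9 months (Table 1).

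**Assumptions (not in the document).** Linear (trapezoid) interpolation between readings; no utility difference at baseline; the between-arm differences d3, d6 and d9 at months 3, 6 and 9.

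**Areas, in utility-months**

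- With month 3: 3(0 + d3)/2 + 3(d3 + d6)/2 + 3(d6 + d9)/2 = 3·d3 + 3·d6 + 1.5·d9
- Without month 3: 6(0 + d6)/2 + 3(d6 + d9)/2 = 4.5·d6 + 1.5·d9
- Error from omitting month 3: 1.5·d6 − 3·d3

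The gain is understated only if d3 exceeds half of d6, unbiased if d3 equals half of d6, and overstated if d3 is smaller.

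**Difference held at D from month 6 to month 9.** Put d3 = f·D and d6 = d9 = D. The area is (4.5 + 3f)·D with month 3 and 6.0·D without.

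| Share f of the month-6 effect present at month 3 | With month 3 | Without | Error |
|---|---|---|---|
| 1 | 7.5D | 6.0D | 20% under |
| 0.75 | 6.75D | 6.0D | 11% under |
| 0.5 (linear rise to month 6) | 6.0D | 6.0D | 0% |
| 0.25 | 5.25D | 6.0D | 14% over |
| 0 | 4.5D | 6.0D | 33% over |

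For a given incremental cost, the cost per QALY is 25% too high at f = 1 (7.5/6.0 = 1.25) and 25% too low at f = 0 (4.5/6.0 = 0.75).

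**Early gain that wanes (d3 = 1)**

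- d6 = 0.75, d9 = 0.5: 6.0 with, 4.125 without, 31% under
- d6 = 0.5, d9 = 0.5: 5.25 with, 3.0 without, 43% under
- d6 = 0.5, d9 = 0: 4.5 with, 2.25 without, 50% under

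**Limit of the remedy.** If the full gain were immediate and held, the true area would be 9D. The present schedule gives 6D (33% under) and adding month 3 gives 7.5D (still 17% under).

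**Precision of the time-averaged quality-of-life effect.** With r post-baseline readings, baseline adjustment and an assumed exchangeable correlation ρ, the variance factor is (1 + (r − 1)ρ)/r − ρ².

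| ρ | r = 2 | r = 3 | Variance cut |
|---|---|---|---|
| 1/3 | 0.556 | 0.444 | 20% |
| 0.6 | 0.440 | 0.373 | 15% |
| 0.7 | 0.360 | 0.310 | 14% |

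In standard error this is a cut of about 7% (1 − √(0.310/0.360)) to 11% (1 − √(0.444/0.556)).

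**The case against.** A reader might infer that the QALY gain is understated by 20% or more, on the view that coaching acts early. There is some support for taking the 20% case as a reference: the planned secondary-outcome model has an intervention term and a time factor with no stated interaction, which amounts to one effect common to all post-baseline visits. But a working model is not a prediction. The Intervention section does not say when goal setting takes place. It describes coach contact over the whole study and nudges learned from each participant's behaviour, which fits a gradual or delayed gain equally well. With no time course or interpolation rule in the document, 20% is neither a floor nor certain in direction. This objection stands in full.

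It is also fair to say that the schedule is stated clearly, that nothing in the visible text contradicts it, and that a mixed model runs on two post-baseline readings. The precision gain is modest, concerns an outcome on which the sample size is not based, and comes with a small change of estimand, since the average would then run over months 3, 6 and 9 and not 6 and 9 alone.

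Finally, recruitment began on 17 February 2023, and the number of participants already past month 3 is unknown. Concurrent 1:1 allocation should spread them over both arms, but balance creates no data: any imputed month-3 values would be borrowed from later enrolees.

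What remains is that the missing reading cannot be recovered at analysis, while collecting it costs little because the contact already exists.

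**Conclusion.** The point holds as a cheap improvement, not as an error in the plan. The QALY estimate depends on an unobserved 0-6 month path. Under linear interpolation, the plausible paths tried here run from about 50% understated (early gain that wanes), through zero (linear rise to month 6), to 33% overstated (no effect until after month 3). The direction cannot be settled from the document, and that indeterminacy is the reason to measure.

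The variance reduction of about 14-20% does not depend on the direction of the bias, but it rests on the assumed exchangeable correlation of 0.33-0.7. Only one secondary outcome and the cost-utility analysis are affected.

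**What to change.** Change the quality-of-life row of Table 1 to "Baseline, 3, 6, and 9 months" and give EQ-5D-5L with the existing month-3 survey to participants who have not yet reached it. For those already past month 3, treat the value as missing: the mixed model can accommodate this for the quality-of-life outcome, and multiple imputation can supply it for the QALY area.

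In either case, report a sensitivity analysis of the QALY result over the assumed month-3 fraction f, using (3f·d6 + 3·d6 + 1.5·d9)/12 for the QALY difference, with f from 0 to 1 and above 1 to cover a gain that wanes. If no participant can still be surveyed at month 3, this analysis and a stated reason for the omission are what remain possible.

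Cost: a small added survey burden, a minor amendment, and no month-3 value for early enrolees.
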